## Abstract

**Background: **The National Integrated Care Programme for Older People (NICPOP), formerly NCPOP aims to support older people to live well in their homes by developing primary and secondary care services for older people, especially those with complex needs. The programme develops integrated intermediate care which traverses both hospital and community settings through multidisciplinary and interagency teams. This team-based approach to the integration of health services is a novel innovation in Irish health service delivery and will require, over time, a shift in cultures of care to allow for the development of competencies for inter-professional collaboration across the care continuum.

The ECLECTIC project will develop an implementation framework for achieving, maintaining and monitoring competencies for interprofessional collaboration among multi-disciplinary teams charged with delivering care for older people across the continuum from acute to community settings.

**Design: **The ECLECTIC research design has been developed in collaboration with the NICPOP. In phase one of the project, a co-design team will collaborate to define and shape competencies for interprofessional collaboration. Phase two will involve the delivery of a collective leadership intervention over a 10-month period with multidisciplinary professionals working with older people across two geographical regions (Mullingar/Midlands and Beaumont/Dublin North). Each group will comprise of members of two multidisciplinary teams charged with coordinating and delivering care to older people across the continuum of acute to community care. Observations of collaborative inter-professional working will take place before, during, and after intervention. In phase three of the study, analysis of the interview and observation data will be presented to the co-design team in order to develop an implementation framework for future teams.

**Discussion:** The co-design process will develop core competencies and performance indicators for collaborative interprofessional working. The resulting implementation framework will be implemented nationally as part of the NICPOP.

## Introduction

Over the next 30 years the number of people in Ireland aged 65 and older is projected to increase by 60–64% and the numbers aged 85 and older by 89–94% (
[name] *et al.*, 2018b). The health system will, therefore, have to respond to this changing demographic and their specific healthcare requirements (
Ireland, 2017;
McLoughlin, 2014;
Office, 2013;
O’Donnell *et al.*, 2019). The National Integrated Care Programme for Older Persons (NICPOP) aligns the programmes of work of the National Clinical Programme for Older People (NCPOP) and the Integrated Care Programme for Older People (ICPOP) under the leadership of [name] (National Clinical Advisor and Group Lead – HSE). It is a joint initiative between the Clinical Strategy and Programmes Division of the Health Service Executive (HSE) and the Royal College of Physicians of Ireland (RCPI) (Executive). The aim of the NICPOP is to improve and standardise the quality of health and social care for older people in Ireland by supporting the provision of services across all settings. The necessity to develop and support interprofessional collaboration in the case management of older people’s care has been identified as a key enabler for improving health and social care delivery. As such, the Inter-Professional Interest Group, a sub-committee of the NICPOP, was established to inform the strategic development of improved collaborative interprofessional working across the boundaries of acute to community health and social care with respect to older people.

Integrated Care (IC) has been adopted in Irish health and social care policy as a strategy for improving the coordination of health and social services across the continuum from acute to community care (
[name] *et al.*, 2018b). Research evidence indicates that models of IC may enhance patient satisfaction, increase perceived quality of care and, importantly in the context of increasing demand, enable improved access to services (
Baxter *et al.*, 2018).
*SláinteCare* is the first Irish health and social care policy to receive cross-party commitment guaranteeing a 10-year implementation plan (
SláinteCare, 2017). The report orientates the health system towards universal access and proposes the development of a new model of coordinated health and social care shifting the focus of service delivery from acute to community. IC is central to this vision as it emphasises cross-agency and multidisciplinary case management and improves access to care in the community.

Aligned to the shifting of focus of older people’s care from the acute-centric model is the intention to establish integrated intermediate care which traverses the hospital and community in the form of multidisciplinary and interagency teams. A total of thirteen pioneer Integrated Care Teams (ICTs) were established within the nine HSE Community Healthcare Organisations (CHOs) which govern service delivery in local communities across the country. The implementation of the ICTs saw the establishment of new community roles for health and social care professionals to engage in a team-based case management approach to coordinating care of older people (
Executive, 2018). This team-based approach to the integration of health services is a novel innovation in Irish health service delivery and will require over time a shift in cultures of care to allow for the development of competencies to foster inter-professional collaboration across the care continuum.

*Our working definition of ICTs follow the European Competency Framework for Health and Social Care Professionals (
Dijkman *et al.*, 2016) and includes all professions working along the continuum of care for older people. In the Irish context, this can include inter alia people working within Emergency Departments’ Frailty Intervention Therapy Teams, Community Health Organisations, Primary Care Teams, Safeguarding and Protection Teams, Mental Health Teams. These teams encompass all health and social care disciplines including nursing and pharmacy.*

The European Competency Framework for Health and Social Care Professionals (HSCPs) working with older people (
Dijkman *et al.*, 2016) describes the outcomes that HSCPs are expected to achieve and demonstrate in their different roles (7 roles in total). The framework describes a minimum set of competencies (18 in total) that constitute a common baseline for HSCPs working with older people and their families within their local communities (
Dijkman *et al.*, 2016). Each of the role-specific competencies is presented with performance indicators that are skills, behaviours or practices that demonstrate competence. This framework, alongside the Irish educational framework for gerontological nursing (
Coffey *et al.*, 2016) will provide a foundation for ECLECTIC in building an understanding of core competencies for inter-professional collaboration across HSCPs. These competencies will be aligned to indicators of appropriate skills, behaviours and practices fostering collaborative working and collective leadership within multidisciplinary teams charged with integrating health and social care for older people in their communities.

While a strategic emphasis on IC is currently at the centre of the Irish health and social care policy, clarity is required regarding the aims of integration, what services are included, which professionals should be involved and how interagency collaboration is occurring (
Cameron *et al.*, 2014;
Shaw *et al.*, 2011). Internationally the literature points to cultural and structural barriers to inter-professional collaboration across the continuum of care (
Ahmed *et al.*, 2015;
[name] *et al.*, 2018b). More specifically, there is a knowledge gap concerning how different health and social care professionals can foster new ways of collaborative working which are foundational to the implementation of IC cultures (
Ahmed *et al.*, 2015;
Cameron *et al.*, 2014). At the centre of the drive for greater integration of services is inter-professional collaboration along a continuum of care (
[name] *et al.*, 2018b;
Van der Heide *et al.*, 2018). Therefore, if the policy agenda on integration is to be realised, it is necessary to understand the competencies and cultures that underpin collaborative approaches to care. This requires a reconceptualisation of leadership and roles within teams responsible for healthcare management and service delivery.

The collective approach to leadership has been defined as a dynamic team phenomenon, where leadership roles are distributed and shared among the team (
D’Innocenzo *et al.*, 2016). This approach requires individuals to adopt leadership roles where they have the expertise and motivation (
Friedrich *et al.*, 2009). Collective and shared approaches to leadership have been found to enhance team effectiveness and team performance outcomes (
D’Innocenzo *et al.*, 2016;
Wang *et al.*, 2014). There is now considerable evidence for the effectiveness of collective leadership interventions in healthcare settings (
De Brún *et al.*, 2019). These studies have indicated the positive impact of collective leadership interventions on staff engagement, quality improvement, team-working and patient satisfaction (
De Brún *et al.*, 2019). Given this evidence base, there have been calls to move from traditional models to shared and distributed models of leadership in healthcare settings where increasingly, care is delivered via multidisciplinary teams (
West *et al.*, 2014;
West *et al.*, 2015).

Effective teamwork is pertinent to inter-professional collaboration, especially for IC. There is limited guidance in the literature regarding how inter-professional collaboration could be fostered and sustained. Collective leadership, given its focus on harnessing collective intelligence towards collective action, and taking collective responsibility for shared impact, seems an appropriate mechanism by which multidisciplinary healthcare teams can demonstrate interprofessional collaboration through improving communication, team-working, person-centred care, and role clarity.

‘Collective Leadership and Safety Cultures’ (Co-Lead) is a 5-year mixed method research and capacity building programme led by [name] (co-author) (
McAuliffe *et al.*, 2017). The Co-Lead curriculum has been co-designed by healthcare staff, patient representatives and researchers (
Ward *et al.*, 2018). The programme involves a series of team-based training modules which aim to develop a dynamic leadership culture within multidisciplinary healthcare teams. Rather than starting from a top-down competency framework-driven curriculum targeted at the individual as leader, development is informed through a bottom-up service needs driven co-designed curriculum targeted at team members as co-leaders (
Ward *et al.*, 2018).

The ECLECTIC project will implement the Co-Lead intervention with multidisciplinary teams working with older people across acute and community care settings. The teams will be observed undertaking this intervention in order to gain insight into how multi-disciplinary teams collaborate when coordinating and delivering IC for older people. Six Co-Lead modules have been selected by the project team for implementation:

1. Team Values, Vision, and Mission2. Team Goal Setting3. Role Clarity4. Collective Leadership for Safety Skills5. Enhancing Person-centred Care6. Monitoring and Communicating Safety Performance at Team Level

We hypothesise that these modules will enable teams to demonstrate the competencies for inter-professional collaboration, as determined by the co-design process.

### Study aim

We aim to collaborate with knowledge users, including public and patient representatives, in defining the core competencies for inter-professional collaborative working in health and social care teams providing services to older people.

The primary outcome of this project will be an implementation guide that details the core competencies for collaborative inter-professional working and provides a framework for achieving, maintaining and monitoring these competencies within multidisciplinary teams working across the continuum of IC for older people.

Specific objectives are:

1. To co-design competencies and performance indicators for inter-professional collaboration, building on the European Competency Framework for HSCPs working with Older People and the Irish educational framework for gerontological nursing.2. To co-design with public and patient representatives (PPRs) two qualitative interview guides and two simulated scenarios/case studies. These will be used as data collection materials when observing ICT members’ approaches to patient care before, during and after the collective leadership interventions.3. To implement six Co-Lead modules and evaluate their efficacy in fostering inter-professional collaboration among the ICTs.4. To provide an implementation framework for achieving, monitoring and sustaining ways of collaborative inter-professional working which will be implemented nationally as part of the Integrated Care Programme for Older People.

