The co-design workshops will build incrementally towards the development of consensus on descriptors of core competencies for inter-professional collaboration as well as performance indicators which will identify measurable skills, behaviours and practices. The European Competency Framework for HSCPs working with Older People (
Dijkman *et al.*, 2016) will provide the building material for the first co-design meeting, facilitating discussion of the characteristics of cohesive health care teams and the shaping of core competencies for collaboration. These competencies will be aligned with measurable outcomes and performance indicators (Objective One).

The second workshop will focus on identifying performance indicators of team cohesion, collective leadership and collaboration within and across healthcare settings relevant to the integration of care for older people. Anticipated output includes core measurable competencies for inter-professional collaborative working, identifying measurable outcomes and indicators of performance. These competencies will be mapped to the content and focus areas of the six Co-Lead modules.

In the third workshop, the co-design team will develop a qualitative interview guide and simulation scenarios for the purpose of generating qualitative observations of team approaches to patient care. The aim of the interview guide will be to prompt individual team members to explore and discuss their understandings of the necessary competencies for multidisciplinary and collaborative working and the performance indicators that they would recognise as being aligned to these competencies. Multidisciplinary simulation is a recognised pedagogical strategy for the development of clinical skills and the evaluation of team performance in the absence of patient risk (
Maxson *et al.*, 2011;
Rodehorst *et al.*, 2005). A multidisciplinary approach to simulation has been used to successfully explore team roles and improve clinical case management (
Rodehorst *et al.*, 2005). The co-design team will develop simulation scenarios from their own practice experience which will be presented to the two ICTs before and after the collective leadership intervention. These scenarios will facilitate observation of the clinical case management approach of the ICTs in relation to competencies for inter-professional collaboration.

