***Work Package Two*** aims to observe in vivo the competencies and performance indicators developed by the co-design process, within the real-world contexts of two multi-professional teams delivering care to older people across the acute and community setting. This will be achieved through implementing a collective leadership intervention over a 10-month period. Two study sites, rural and urban (Mullingar/Midlands and Beaumont/Dublin North), have been identified. Each team will be multidisciplinary in their composition, represent acute as well community care settings and will be working together to provide care for the same patients. Observing the teams before, during, and after intervention will allow for the comparison of contextual information pertaining to team cohesion and collaboration from an urban and rural location.

The sampling allows for comparisons between a pioneer ICT operating under NICPOP and a multi-disciplinary team who are operating across the boundary of community and acute care but who are not formally a part of the NICPOP. This will be important for the planned implementation of the ECLECTIC study findings within the NICPOP and more specifically for plans to develop further ICTs throughout the country. In order to champion this project within the two sites and to facilitate access to the relevant teams, representatives from the acute and community settings for both teams are included as members of the project team (AC, LL and PM – hospital representatives; NB and PR – community representatives).

Work Package Two will be a five-step process involving the gathering of qualitative empirical data through semi-structured interviews, observations of team approaches to simulated scenarios as well as ethnographic observations of the teams engaging with six Co-Lead modules (Objective Three). It will commence with semi-structured qualitative interviews of individual team members from both sites. Exploratory qualitative investigation is appropriate for this component of the project as little is known about how individual team members interpret and understand inter-professional collaboration in relation to their own disciplinary competency as well as in relation to the integration of patient centred care.

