Following completion of the six modules, qualitative exploration of the teams in relation to the operationalising of competencies for inter-professional collaboration will be repeated. Semi-structured interviews with each of the team members will be undertaken in order to explore how the collective leadership intervention have impacted upon their understanding of inter-professional collaboration and the integration of patient-centred care. The teams will be observed again in their approach to simulated scenarios that represent the complexities of integrating care for older people along a continuum from acute to community settings. The observations will focus on the operationalising of competencies for inter-professional collaboration in relation to simulated case management. The analysis of the qualitative data generated from this repeat wave of interviews and observations will evaluate the impact of the collective leadership intervention on an evolving team understanding of competencies for collaboration. Contextual information on how competencies are operationalised in terms of performance indicators and team cultures will be gathered to inform the implementation framework which will be the focus of the third work package.

***Work Package Three*** aims to develop an implementation framework for achieving, monitoring and sustaining ways of collaborative interagency working. This framework will be adopted by the NICPOP and used to support implementation at service delivery level. The framework will present the agreed core competencies for inter-professional collaborative working and align these competencies with measurable outcomes and performance indicators. There will be clear recommendations provided in the implementation strategy of the framework which will guide the NICPOP as to the application of the competencies and performance indicators within the national programme of ICTs for older people.

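### Objective 3 promises to evaluate the efficacy of the Co-Lead modules, but every team receives them and nothing serves as a control, so the study can only describe change

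*Protocol article*

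**What the plan says.** Three places in the protocol article use causal wording about the modules:

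- Study aim, Objective 3: "To implement six Co-Lead modules and evaluate their efficacy in fostering inter-professional collaboration among the ICTs".
- Introduction, after the list of modules: "We hypothesise that these modules will enable teams to demonstrate the competencies for inter-professional collaboration".
- Methods, Procedure, Work Package Two: analysis of the repeat interviews and observations "will evaluate the impact of the collective leadership intervention on an evolving team understanding of competencies for collaboration".

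The design is in the Work Package Two text. The work is set "within the real-world contexts of two multi-professional teams delivering care to older people across the acute and community setting", and the article adds: "This will be achieved through implementing a collective leadership intervention over a 10-month period". Team members are interviewed and the teams are observed on simulated cases. The teams then take the six modules while field notes are kept, after which the interviews and simulations are repeated. The ethics section says that randomisation is not used. The Study aim section names an implementation guide as the primary outcome.

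**The concern.** Efficacy is a causal term. To evaluate it, a study needs some basis for saying what would have happened to the same teams without the modules. The plan describes none. If the objective stands, a favourable repeat wave could be reported as showing that Co-Lead works, when the data would show only that something changed while Co-Lead was being delivered. This matters because the project's framework is meant for national use and is to say how the competencies can be achieved. An efficacy statement in the same report would carry weight that the study had not earned.

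**Working it through.** No arithmetic applies. The article states no sample size, effect size, error rate or quantitative outcome for the modules, so there is no figure to reproduce. The check compares what the objective needs with what the design supplies.

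1. **Who receives the modules?** Work Package Two sends both teams through them after the first round of data collection. No untreated, delayed-start or historical comparator is described.

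2. **Is there allocation by chance?** No; the ethics section rules it out.

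3. **Can the between-team contrast act as a control?** Work Package Two sets a pioneer integrated care team against a team outside the national programme, at one rural and one urban site. Both are treated, so the contrast says nothing about the absence of treatment. With two teams at two sites there is one team per level. Programme status and location therefore coincide and cannot be separated either.

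4. **Does the number of teams matter?** The Abstract is less clear than the Methods: "Each group will comprise of members of two multidisciplinary teams" could be read as up to four teams over the two regions. All would still receive the modules, so the conclusion is the same on either reading.

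5. **What remains is each team against its own past.** At least three other explanations stay open:
   - *Other service change.* The teams work in real services during a period of integrated-care reform. Nothing in the design removes the effect of concurrent change.
   - *Repeat exposure to simulation.* Teams meet simulated cases before and after the modules. Work Package One says: "Multidisciplinary simulation is a recognised pedagogical strategy for the development of clinical skills". The same sentence goes on to name evaluation of team performance as a second use. So the article's own account allows that the first session may build skill as well as measure it.
   - *Being observed and interviewed.* Teams are watched before, during and after, and members are interviewed about collaboration. This alone may alter what they say and do.

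6. **Can the qualitative data close the gap?** Interviews can report what members believe changed and why. Field notes can show how a change unfolded. Both are useful, but neither shows the course of a team without the modules.

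The objective therefore claims a property that the design lacks.

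**The case against.** The best defence is that this is a qualitative, developmental study, and that one word is being read too literally. Work Package Two is introduced as observing the competencies in practice. The later interviews are meant to explore how members' understanding was affected. The impact sentence concerns an evolving understanding rather than measured performance. The hypothesis specifies no comparative test, and the primary outcome is a guide rather than an effect estimate. Observation during each module, and the attention to contextual influences in Work Package Three, are what a qualitative evaluation uses to judge how change arose. A journal article also condenses a fuller protocol.

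Much of this stands, and it limits the point to the claim: the design suits the guide and does not need to be rebuilt. It does not rescue Objective 3. Process and contextual evidence can make an account of change more or less plausible, but it does not supply a comparison. The softer passages also show that the article already has the right language available and departs from it in the objective. Condensation is no answer, because a stated objective is being set against a stated design.

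**Conclusion.** The point holds, at moderate severity. Objective 3 as worded cannot be met by an uncontrolled study, observed before, during and after, in which all teams are treated. The study can support statements about perceived change and observed change, but not about efficacy. This rests on the article's description that both teams take the modules and that no comparator exists. It does not depend on whether there are two teams or four.

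A reader might infer more than the documents support:

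- *That the plan forecasts a background shift in care cultures.* The Abstract and Introduction say that integration will require such a shift over time. That is a condition for success, not a prediction. Service change is a possible rival explanation, not one that the plan announces.
- *That the baseline simulation is training.* The article names both skill development and evaluation as uses, and describes presenting cases and observing the teams. A practice effect is possible but not established.
- *That ten months is the problem.* This is the delivery period. The missing comparator is the reason efficacy cannot be shown, and a different length would not cure it.
- *That a chance of a false success can be calculated.* The article defines no improved-or-not outcome, no rule for declaring success and no background rate, and the teams need not change independently. Any such percentage would be invented.
- *That national adoption of Co-Lead depends on Objective 3.* The described framework consists of competencies, indicators, a process model and guidelines. No passage makes roll-out of the modules conditional on this result.

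**What to change.** Four changes of wording:

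1. Reword Objective 3 as: *implement six Co-Lead modules and explore perceived change, and describe observed change, in inter-professional collaboration*.
2. In the Work Package Two text on the repeat wave, replace the promise to evaluate impact with *explore change following* the intervention.
3. In the Introduction, present the hypothesis as an expectation to be explored.
4. State that the final report and the framework will not present the modules as having shown efficacy.

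Optional additions are an interview question inviting other explanations for any change, and a short log of concurrent service changes. Both would strengthen the description, but the point does not depend on them.

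The cost is a less favourable stated claim. Sites, data collection and the primary outcome are untouched. The article says that the study began in September 2019, but the wording of the objective and the limits on reporting can still be corrected. Keeping the efficacy claim would instead need an untreated or delayed-start comparator and more teams, which is a different and much larger study.
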